# Administrative rules

## Curriculum Vitae

An updated copy of the curriculum vitae limited to the experience, qualification and training for each Investigator and Sub-Investigator will be provided to the Sponsor prior to the beginning of the Clinical Trial.

## Record retention in study site(s)

The Investigator must maintain confidential all study documentation, and take measures to prevent accidental or premature destruction of these documents.

It is recommended that the Investigator retain the study documents at least fifteen (15) years after the completion or discontinuation of the Clinical Trial, unless otherwise specified in the Investigator Agreement in line with national standards and/or local laws.

However, applicable regulatory requirements should be taken into account in the event that a longer period is required.

The Investigator must notify the Sponsor prior to destroying any study essential documents following the Clinical Trial completion or discontinuation.

If the Investigator's personal situation is such that archiving can no longer be ensured by him/her, the Investigator shall inform the Sponsor and the relevant records shall be transferred to a mutually agreed upon designee.

# Confidentiality

All information disclosed or provided by the Sponsor (or any company/institution acting on their behalf), or produced during the Clinical Trial, including, but not limited to, the Clinical Trial Protocol, the CRFs, and the results obtained during the course of the Clinical Trial, is confidential. The Investigator and any person under his/her authority agree to undertake to keep confidential and not to disclose the information to any third party without the prior written approval of the Sponsor.

However, the submission of this Clinical Trial Protocol and other necessary documentation to the Faculty of Medicine Makerere University Research and Ethics Committee (FOMREC), Uganda National Council of Science and Technology (UNCST), the Uganda National Drug Authority, (NDA)is expressly permitted, their members having the same obligation of confidentiality.

The Sub-Investigators shall be bound by the same obligation as the Investigator. The Investigator shall inform the Sub-Investigators of the confidential nature of the Clinical Trial.

The Investigator and the Sub-Investigators shall use the information solely for the purposes of the Clinical Trial, to the exclusion of any use for their own or for a third party's account.

# Property rights

All information, documents and Investigational Product provided by the Sponsor or its designee are and remain the sole property of the Sponsor.

The Investigator shall not mention any information or the Product in any application for a patent or for any other intellectual property rights.

All the results, documents and inventions, which arise directly or indirectly from the Clinical Trial in any form, shall be the exclusive property of the Sponsor.

The Sponsor may use or exploit all the results at its own discretion, without any limitation to its property right (territory, field, continuance). The Sponsor shall be under no obligation to patent, develop, market or otherwise use the results of the Clinical Trial.

# Data protection

The patient's personal data and Investigator's personal data which may be included in the Sponsor database shall be treated in compliance with all applicable laws and regulations.

When archiving or processing personal data pertaining to the Investigator and/or to the patients, the Sponsor shall take all appropriate measures to safeguard and prevent access to this data by any unauthorized third party.

# Insurance compensation

The Sponsor certifies that it has taken out a liability insurance policy covering all clinical trials under its sponsorship. This insurance policy is in accordance with local laws and requirements. The insurance obtained by the sponsor does not relieve the Investigator and the collaborators from maintaining their own liability insurance policy. A copy of the insurance certificate will be provided to the Ethic Committees/IRBs or CA in countries requiring this documentation.

# Sponsor audits and inspections by regulatory agencies

For the purpose of ensuring compliance with the Clinical Trial Protocol, Good Clinical Practice and applicable regulatory requirements, the Investigator should permit auditing by or on the behalf of the Sponsor and inspection by applicable regulatory authorities.

The Investigator agrees to allow the auditors/inspectors to have direct access to his/her study records for review, being understood that this personnel is bound by professional secrecy, and as such will not disclose any personal identity or personal medical information.

The Investigator will make every effort to help with the performance of the audits and inspections, giving access to all necessary facilities, data, and documents.

As soon as the Investigator is notified of a future inspection by the authorities, he will inform the Sponsor and authorize the Sponsor to participate in this inspection.

The confidentiality of the data verified and the protection of the patients should be respected during these inspections.

Any result and information arising from the inspections by the regulatory authorities will be immediately communicated by the Investigator to the Sponsor.

The Investigator shall take appropriate measures required by the Sponsor to take corrective actions for all problems found during the audit or inspections.

# Premature discontinuation of the study or premature close-out of a site

## Decided by the Sponsor in the following cases:

If the information on the product leads to doubt as to the benefit/risk ratio;

If the Investigator has received from the Sponsor all Investigational Product, means and information necessary to perform the Clinical Trial and has not included any patient after a reasonable period of time mutually agreed upon;

In the event the results of the Clinical Trial do not appear to be scientifically convincing to the Sponsor (for example based on the results of a planned futility analysis);

If the aim of the Clinical Trial has become outdated or is no longer of interest;

In the event of breach by the Investigator of a fundamental obligation under this agreement, including but not limited to breach of the Clinical Trial Protocol, breach of the applicable laws and regulations or breach of the ICH guidelines for Good Clinical Practice;

In any case the Sponsor will notify the Investigator of its decision by written notice.

## Decided by the Investigator

The Investigator must notify (at least 30 days prior to discontinuation) the Sponsor of his/her decision and give the reason in writing.

In all cases (decided by the sponsor or by the Investigator), the Faculty of Medicine Makerere University Research and Ethics Committee (FOMREC), Uganda National Council of Science and Technology (UNCST), the Uganda National Drug Authority, (NDA) should be informed.

# Clinical trial results

The Sponsor will be responsible for preparing a Clinical Study Report;

When the data from all investigational sites have been fully analyzed by the Sponsor, the latter will communicate the results of the Clinical Trial to the Investigator(s);

Regardless of the study outcome the Sponsor is committed to publish the results.

# Publications and communications

## Publication/communication of study results

The Sponsor recognizes the Investigator's right to utilize data derived from the clinical trial for teaching purposes, communication at congresses and scientific publications. Nevertheless, in order to ensure the accuracy and scientific value of the information, while preserving the independence and accountability of the Investigator, and the confidentiality of the information, only checked and validated data will be used. To that effect, it is essential that the parties exchange and discuss, prior to any publication or communication, any draft publication or communication made by the Investigator.

The Investigator shall send to the Sponsor a copy of the manuscript for review and possible comments at least forty-five (45) calendar days in advance of the date of submission to the journal and at least twenty (20) days in advance for abstracts. The publication shall be delayed until a written response is received by the Sponsor, not to exceed ninety (90) days The Sponsor can delay publication or communication for a limited time in order to protect the confidentiality or proprietary nature of any information contained therein, it being understood that the Sponsor cannot refuse its consent without reasonable cause. The Investigator agrees to include the modifications requested by the Sponsor, provided they do not jeopardize the accuracy and/or the scientific value of the publication.

The study results must be submitted to the review of the Steering Committee before publication. All study investigators and Committee members give full authority to the Steering Committee for primary presentation and/or primary publication of results. However in absence of primary publication within 12 months of the termination of the clinical trial at all other sites, the Sponsor or the Steering Committee if applicable may consider investigator’s request for independent publication..The Investigator agrees not to publish the results of the clinical trial pertaining to his/her center prior to the publication of the overall clinical trial results. If no publication has occurred within twelve (12) months of the termination of the clinical trial at all other sites, the Investigator shall have the right to publish independently the results of this clinical trial, patient to the review procedure set forth herein. If the clinical trial is conducted with the support of a Steering Committee, the latter may define specific rules for publication.

No other publication is allowed before the primary publication. Any subsequent presentation or publication by a study participant (including for substudies) must be approved by the Sponsor and make reference to the study and the primary publication.

The Investigator shall not use the name(s) of the Sponsor and/or its employees in advertising or promotional material or publication without the prior written consent of the Sponsor. The Sponsor shall not use the name(s) of the Investigator and/or the collaborators in advertising or promotional material or publication without having received his/her and/or their prior written consent(s).

The Sponsor has the right at any time to publish the results of the clinical trial.

## Public disclosure of clinical trials

Regarding clinical trial registries, sanofi-aventis will comply with the following:

- This clinical trial will be recorded in a registry accessible to the public free of charge; Sanofi-aventis has decided to register its clinical trials on the following web site: [www.clinicaltrials.gov](javascript:go_out_ext('http://www.clinicaltrials.gov');).
  - The registry will contain basic information about each trial sufficient to inform interested patients (and their healthcare practitioners) how to enrol in the trial;
  - The trial will be registered under a unique identification number to ensure transparency of clinical trial results;
  - As a general rule, clinical trial information will be published within 21 days following enrolment of the first patient.
- The results of this clinical trial will be published in a database accessible to the public free of charge; Sanofi-aventis has decided to publish the results of its clinical trials on the following web site: [www.clinicalstudyresults.org](javascript:go_out_ext('http://www.clinicalstudyresults.org');)
  - If trial results are published in a peer-reviewed medical journal, the database will contain a citation to or link to the journal article and/or a summary of the results in a standard format, such as the ICH E-3 summary format, that includes a description of the trial design and methodology, results of primary and secondary outcome measures, and safety results. Study results will be recorded in a database in the ICH E-3 format if they are not published in a medical journal within required time frame;
  - Results will include the unique identification number used to register the corresponding trial;
  - As a general rule, results will be published within one year of trial completion, unless such publication would compromise publication in a peer-reviewed medical journal or contravene national laws or regulations.

In case of local requirement, additional registration at local registries may also be done by sanofi-aventis.

# Clinical trial protocol amendments

All appendices attached hereto and referred to herein are made part of this Clinical Trial Protocol.

The Investigator should not implement any deviation from, or changes of the Clinical Trial Protocol without agreement by the Sponsor and prior review and documented approval/favorable opinion from the Faculty of Medicine Makerere University Research and Ethics Committee (FOMREC), Uganda National Council of Science and Technology (UNCST), the Uganda National Drug Authority, (NDA)of an amendment, except where necessary to eliminate an immediate hazard(s) to Clinical Trial Patients, or when the change(s) involves only logistical or administrative aspects of the trial. Any change agreed upon will be recorded in writing, the written amendment will be signed by the Investigator and by the Sponsor and the signed amendment will be filed with this Clinical Trial Protocol.

Any amendment to the Clinical Trial Protocol requires written approval/favorable opinion by the Faculty of Medicine Makerere University Research and Ethics Committee (FOMREC), Uganda National Council of Science and Technology (UNCST), the Uganda National Drug Authority, (NDA) prior to its implementation, unless there are overriding safety reasons.

In some instances, an amendment may require a change to the Informed Consent Form. The Investigator must receive an approval/favorable opinion from the Faculty of Medicine Makerere University Research and Ethics Committee (FOMREC), Uganda National Council of Science and Technology (UNCST), the Uganda National Drug Authority, (NDA) concerning the revised Informed Consent Form prior to implementation of the change

# Appendices

APPENDIX 1: WHO guidelines for assessing response to treatment (2003)

APPENDIX 2: Guidelines for grading physical examination findings

APPENDIX 3: Guidelines for grading laboratory results

APPENDIX 4: Criteria for severe malaria / Danger signs

APPENDIX 5: Specific guideline for neutropenia and increase of ALT

APPENDIX 6: Methods of blood sample analyzes

APPENDIX 7: Operational definitions

APPENDIX 8: World Medical Association Declaration of Helsinki

APPENDIX 9: Flow of patients in OPD and Study Clinic

APPENDIX 1Document related to the assessment of judgment criteria

WHO guidelines for assessing response to treatment (2003)

| ETF (Early Treatment Failure):   - Development of danger signs or severe malaria on Days 1or 2 or 3 in the presence of parasitemia - Parasitemia on Day 2 higher than on Day 0, irrespective of axillary temperature - Parasitemia on Day 3 with axillary temperature > 37,5C - Parasitemia on Day 3 > 25% of count on Day 0 |
| --- |
| LCF (Late Clinical Failure):   - Development of danger signs or severe malaria after Day 3 in the presence of parasitemia, without previously meeting any of the criteria of early treatment failure - Axillary temperature > 37,5C ( or history of fever) on any day from Day 4 to 28 in the presence of parasitemia, without previously meeting any of the criteria of early treatment failure |
| LPF ( Late Parasitological Failure):   - Presence of parasitemia on any day from Day 7 to Day 28 and axillary temperature  < 37,5C , without previously meeting any of the criteria of early treatment failure or late clinical failure |
| **ACPR (Adequate Clinical and Parasitological Response)**   - Absence of parasitaemia on Day 28, irrespective of axillary temperature, without previously meeting any of the criteria of early treatment failure or late clinical or parasitological failure |

Appendix 2: Guidelines for grading physical examination findings

|  | **Grade 1**  **MILD** | **Grade 2**  **MODERATE** | **Grade 3**  **SEVERE** | **Grade 4**  **LIFE THREATENING** |
| --- | --- | --- | --- | --- |
| **Subjective fever in the past 24 h** | N/A | Present (Yes) | N/A | N/A |
| ***Weakness*** | Mild decrease in activity, still playing | Moderate decrease in activity, playing limited | Not participating in usual activities, not playing | Lethargic |
| **Muscle and/or joint aches*** | Mild localised complaints | Mild diffuse complaints | Objective weakness; function limited | N/A |
| ***Headache**** | Mild, no therapy required | Transient, moderate; therapy required | Severe; responds to initial narcotic therapy | Intractable; requires repeated narcotic therapy |
| **Anorexia** | Decreased appetite, but still taking solid food | Decreased appetite, avoiding solid food | Refusing to breast feed, appetite very decreased, no solids or liquids taken  (< 2 years < 12 hr;  > 2 years < 24 hr) | Refusing to breast feed, appetite very decreased, no solids or liquids taken  (< 2 years < 12 hr; > 2 years < 24 hr) |
| **Nausea*** | Mild discomfort; maintains reasonable intake | Moderate discomfort; intake decreased significantly; some activity limited | Severe discomfort; no significant intake; activities limited | Minimal fluid intake |
| **Vomiting** | Transient emesis | Occasional or moderate vomiting | Orthostatic hypotension or IV fluids required | Hypotensive shock or hospitalization required for IV fluid |
| **Abdominal pain*** | Mild | Moderate – no treatment needed | Moderate to severe – treatment needed | Severe – hospitalized for treatment |
| **Diarrhea** | Transient 3-4 loose stools/day | 5-7 loose stools/day | Orthostatic hypotension or > 7 loose stools/day or IV fluids required | Hypotensive shock or hospitalization for IV fluid therapy required |
| **Cough** | Transient – no treatment required | Continuous, requires treatment | Uncontrolled | Cyanosis, stridor, severe shortness of breath |
| **Pruritis** | Pruritis without rash | Pruritic rash, pruritis without rash that disturbs sleep | Mild urticaria | Severe urticaria, anaphylaxis, angioedema |
| **Tinnitus*** | Mild ringing or roaring sound | Moderate ringing or roaring sound | Severe ringing or roaring sound with associated hearing loss | N/A |
| **Behavioural changes** | Mild difficultty concentrating; mild confusion or agitation; activities of daily living unaffected; no treatt | Moderate confusion or agitation; some limitation of activities of daily living; minimal treatment | Severe confusion or agitation; Needs assistance for activities of daily living; therapy required | Toxic psychosis; hospitalization required |
| **“Flu”**  **(viral URI)** | Mild nasal congestion, mild rhinorrhea, no cough | Moderate nasal congestion, moderate rhinorrhea, cough present | N/A (if severe, classify individual symptoms) | N/A (if life-threatening, classify individual symptoms) |
| **Convulsion** | N/A | N/A | Localized or generalized seizure | Status epilepticus |
| *** Assess only in children > 3 years of age. Answer N/A for younger children and those unable to answer.** | | | | |

† Reference – Based on WHO Toxicity Grading Scale for Determining the Severity of Adverse Events

**APPENDIX 2b Guidelines for grading physical examination findings (cont.)**

|  | **Grade 1**  **MILD** | **Grade 2**  **MODERATE** | **Grade 3**  **SEVERE** | **Grade 4**  **LIFE-THREATENING** | |
| --- | --- | --- | --- | --- | --- |
| **Temperature* (tympanic membrane)** | 38.0-38.4C | 38.5-40.0C | > 40.0C | Sustained fever, equal or greater than 40.0C for longer than 5 days | |
| **Dehydration**  ****** | Normal skin turgor and touch, moist mucous membranes, tears present, eyes normal, fontanelle flat, CNS – consolable, pulse regular, urine output normal | Skin dry with + tenting, dry mucous membranes, eyes deep set, decreased tears, fontanelle soft, CNS – irritable, pulse slightly increased, urine output decreased | Skin clammy with lack of turgor, parched/cracked mucous membranes, sunken eyes, no tears, sunken fontanelle, CNS – lethargic, pusle increased, no urine output | | |
| **Facial edema** | Present, mild swelling of eyes | Moderate swelling of eyes, face | Severe swelling involving eyes, face, and mucous membranes; unable to open eyes | | Airway compromise |
| **Jaundice** | Slight yellowing of sclera and conjunctiva | Moderate yellowing of sclera and conjunctiva, yellowing of mucous membranes | Severe yellowing of sclera and conjunctiva, yellowing of skin | | N/A |
| **Chest** | Mildly increased RR (for age, temperature), transient or localised adventitious sounds | Moderately increased RR, diffuse or persistent adventitious sounds | Rapid RR (< 2 months > 60, 2-12 months > 50,  1-5 years > 40, adults > 30)*nasal flaring, retractions | | Cyanosis |
| **Abdomen** | Normal bowel sounds, mild localised tenderness, and/or liver palpable 2-4 cm below the right costal margin (RCM), and/or spleen palpable, and/or umbilical hernia present | Normal or mildly abnormal bowel sounds, moderate or diffuse tenderness; and/or mild to moderately enlarged liver (4-6 cm below the RCM) and/or spleen palpable up to half-way between umbilicus and symphysis pubis | Severely abnormal bowel sounds, severe tenderness to palpation. Evidence of peritoneal irritation and/or significant enlargement of liver (> 6 cm below the RCM) and/or spleen palpable beyond half-way between umbilicus and symphysis pubis | | Absent bowel sounds. Involuntary rigidity |
| **Skin†** | Localised rash, erythema, or pruritis | Diffuse, maculopapular rash, dry desquamation | Vesiculation, moist desquamation, or ulceration | | Exfoliative dermatitis, mucous membrane involvement or erythema multiforme or suspected Stevens-Johnson or necrosis requiring surgery |

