### Methods of assessment

- Physical and Clinical signs and symptoms: the following signs and symptoms will be examined systematically by the investigator and described as being absent, mild, moderate, severe or life threatening: weakness, muscle and/or joint aches, headache, anorexia, nausea, vomiting, abdominal pain, diarrhea, cough, pruritus, tinnitus, behavioural changes, flu, convulsion, dehydration, jaundice, chest ,abdomen, skin (cf. Appendix 2 for grading all of them), Hackett splenic score (score from 0 to 5: Appendix 2d)
- Temperature: axillary temperature will be taken using an electronic thermometer
- Blood pressure (SBP, DBP in mmHg), respiratory rate (pm) and pulse rate (bpm) will be measured after resting for 10 minutes in the sitting position.
- Microscopy

Blood samples will be collected from patients for thick and thin blood smears on days 0, 1, 2, 3, 7, 14, 21, 28, 42 and on any unscheduled day that the patient presents with clinical deterioration or recurrent fever. About a drop of blood is collected for each smear. Thick and thin blood smears obtained from fingerpick blood samples will be stained with Giemsa and read by experienced laboratory technologists who are not directly involved in direct patient care. Parasite and gametocyte densities will be calculated from thick blood smears and thin smears will be used for parasite species identification (Appendix 6). Urgent thick smears will be read in our study clinic for initial diagnosis and to identify treatment failures during follow-up. Routine blood smears will be read within 48 hours. For quality control, all slides will be read by a second microscopist and a third reviewer will settle any discrepant readings.

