## Identification of adverse events

At each follow-up visit (days 1, 2, 3, 7, 14, 21, 28, and 42, and any unscheduled day), study clinicians will assess patients according to a standardized clinical record form. A severity grading scale, based on toxicity grading scales developed by the WHO and the National Institutes of Health, Division of Microbiology and Infectious Diseases, will be used to grade severity of all symptoms, physical exam findings, and laboratory results as mild, moderate, severe or life threatening (Appendices 2 and 3). Any new event, or an event present at baseline that is increasing in severity, will be considered an adverse event.

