## Reporting of adverse events

For each possible adverse event identified and graded as mild, moderate, severe or life threatening, an adverse event report form will be completed. The following information will be recorded for all adverse experiences that are reported:

1. Description of event
2. Date of event onset
3. Maximum severity of the event
4. Maximum suspected relationship of the event to study medication
5. Is the event serious?
6. Outcome
7. Date event resolved

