#### Analysis of adverse events

Treatment-emergent AEs (TEAEs) are defined as AEs that developed or worsened during the study period (time from first dose of study medication up to D42 days after the first dose of study medication) for each attack.

All adverse events will be coded using MedDRA. The following frequency distributions of adverse events (incidence tables) will be provided for the safety population:

- All and possibly related TEAEs by system organ class,
- Possibly related TEAEs by system organ class and by decreasing frequency,
- All and possibly related TEAEs by intensity and system organ class,
- Serious adverse events: All and possibly related TEAEs by seriousness criterion,
- Serious adverse events: All and possibly related TEAEs by system organ class,
- Death: All and possibly related TEAEs by system organ class,
- Other significant adverse events: All and possibly related TEAEs by “other significant” adverse event criterion,
- Discontinuation: All and possibly related TEAEs by system organ class,
- Laboratory abnormalities: All and possibly related TEAEs,

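### Appendix 2b defines grade 1 (mild) dehydration only by normal findings, so mild cannot be told apart from absent dehydration

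*Protocol*

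**What the plan says.** Section 10.1.3 (Methods of assessment) names dehydration among the signs to be examined systematically. Each sign is to be "described as being absent, mild, moderate, severe or life threatening", and Appendix 2 is given as the grading reference for all of them. Absent and mild are thus two separate codes.

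The Appendix 2b entry for grade 1 (mild) dehydration opens "Normal skin turgor and touch, moist mucous membranes, tears present, eyes normal, fontanelle flat" and is completed by a consolable child, a regular pulse and normal urine output. The grade 2 (moderate) entry starts "Skin dry with + tenting, dry mucous membranes, eyes deep set, decreased tears".

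The grade is then used in three places. Section 11.4 decides what is an adverse event: "Any new event, or an event present at baseline that is increasing in severity, will be considered an adverse event". Section 11.6 sets the paperwork: "For each possible adverse event identified and graded as mild, moderate, severe or life threatening, an adverse event report form will be completed". Section 14.5.4.1 lists among its tables "All and possibly related TEAEs by intensity and system organ class". The synopsis also has all clinical symptoms graded so that their course from baseline can be followed.

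**The concern.** A severity scale needs its lowest grade to describe something other than the normal state. Here the mild entry describes a child with nothing abnormal on examination, while section 10.1.3 keeps absent as a separate option. Two clinicians who see the same well-hydrated child could tick different boxes, and the written rule supports both.

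Clinical tolerability is a stated secondary comparison for the first attack and for repeated attacks (section 6.2). Dehydration is one of the examined signs that feed it. What is at stake is whether grade 1 dehydration, as a baseline finding or as a mild event, can be reproduced from the protocol. A visit coded without a criterion cannot be recoded afterwards, because the code may be the only record of what was seen.

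**Working it through.** The protocol gives no figure for this point, so the check sets the texts side by side.

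1. **Count the grade 1 descriptors.** There are eight: skin turgor and touch, mucous membranes, tears, eyes, fontanelle, consolability, pulse, urine output. Abnormal: 0 of 8.

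2. **Check that the columns have not slipped.** Grade 2 covers the same eight items and is where abnormal findings first appear; the next cell covers them again in worse form. The sequence is orderly, so the all-normal text does sit under grade 1.

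3. **Compare neighbouring rows.** Grade 1 facial oedema is "Present, mild swelling of eyes", and grade 1 jaundice needs slight yellowing. The abdomen row opens with normal bowel sounds but adds a positive sign. Among these rows, only dehydration has a mild grade with no abnormality.

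4. **Look elsewhere for a criterion.** Section 10.1.3 gives none for absent. The general severity scale in section 11.5 ties mild to a sign or symptom, which the dehydration row does not require. The flow chart marks weight at D0 only, so scheduled weights cannot show a loss. Nothing in the protocol fills the gap.

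5. **Trace the effect.** Take a child whose findings are normal at D0 and stay normal. The two codes are interchangeable under the table, so four patterns are possible:

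| D0 | Follow-up | Result under section 11.4 |
|---|---|---|
| absent | absent | no event |
| mild | mild | present at baseline and not worse: no event |
| mild | absent | apparent improvement: no event |
| absent | mild | nominally a new grade 1 finding |

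Only the last pattern can lead to an event, and under section 11.2 the finding would also have to be judged related to the study drug. If the table is applied literally at every visit, all normal children fall in the second row and grade 1 events tend towards zero. If absent is tried first, the grade 1 count depends on a threshold that each clinician sets alone. Neither use yields a grade 1 that the text defines.

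**The case against.** The strongest reply is that matching a grade does not create an adverse event. Section 11.3 requires an untoward occurrence, section 11.4 a new or worsened one, and section 11.2 also asks for a judged relation to the drug. Section 11.6 speaks of events that are identified and then graded. A sensible clinician scores a well-hydrated child absent and never opens the table. This stands, and it defeats a reading that a reader might infer: that every well child counts as mildly dehydrated in the safety tables.

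Three other strong readings also fail.

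- *Recovery from grade 2 cannot be recorded.* It can: outcome (section 11.5) and date of resolution (section 11.6) are separate fields that do not depend on the Appendix 2 grade.
- *The gap costs a quantifiable amount of power.* That would need a miscoding rate and true dehydration rates, none of which the protocol gives. It would also need a comparison of dehydration alone, which section 14.5.4.1 does not list.
- *Signals of gastrointestinal intolerance are lost.* Vomiting and diarrhoea have their own rows with real grade 1 criteria. Section 11.7 also asks that symptoms be grouped under one diagnosis where possible, so dehydration may often not stand alone.

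The row cites a paediatric handbook that is not at hand. It may allow mild dehydration to be diagnosed without visible signs, for example from history. That cannot be settled here, and the protocol does not say so.

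None of this supplies the missing boundary. The clinician who scores absent is relying on good sense against the table that section 10.1.3 names as the reference.

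**Conclusion.** The point holds as a small defect in what is written. The grade 1 dehydration entry contains no finding that distinguishes it from no dehydration, although section 10.1.3 requires the two to be scored separately with that table. The mild category for this sign, at baseline and in the tables by intensity, is therefore not reproducible from the protocol.

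Its reach is one sign at one grade. Dehydration of grade 2 and above is kept apart in the by-intensity table and is untouched. The primary endpoint and the sample size do not depend on it. It would go too far to say that the dehydration data mean nothing.

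The conclusion rests on the protocol text alone and assumes that no case report form instruction outside it already defines the boundary.

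**What to change.** Reconcile Appendix 2b with sections 10.1.3 and 11.4 in one of two ways:

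- relabel the all-normal set as absent (grade 0); or
- have the investigators state in the grade 1 cell what distinguishes mild from absent dehydration.

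In either case, state that D0 and follow-up visits are coded by the same rule, so that new or worsened can be derived from the codes.

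The cost is one table cell and a note in the case report form instructions. The first option has one drawback: dehydration suspected without visible signs would no longer be captured as mild by this row. If the investigators want to keep such cases, the second option does so, provided the basis for the judgement is written down. The change concerns recording only and leaves the management of patients as it is.
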